## Discussion

Ankle sprain has a high recurrence rate, and repeated sprain often progress into CAI. TCC is an ancient form of physical activity that originated in China and has become widely popular around the world. Even though the benefits of practicing TCC have been proven in different populations, to date there are not enough qualified studies to confirm the clinical effect of TCC exercise on balance ability and ankle instability in subjects with CAI. This study aims to determine the effect of 12 weeks of TCC intervention on postural stability and self-reported outcomes in patients with FAI. At the same time, the superiority of its clinical efficacy will also be compared with that of CBT.

Considering that CAI may limit the sensorimotor system, which may further limit the ability to maintain posture control (27). Commonly used rehabilitation balance programs are reported to improve “proprioception,” which means that they may have a positive effect on the somatosensory system (28, 29). Moreover, as mentioned above, CBT can improve ankle function and increase ankle stability, which has been confirmed by a number of studies (1, 13, 30).

In TCC practice, the slow, gentle, rhythmic movements are connected together in a continuous sequence, and movement transitions, center of gravity shifts, and posture transitions are all closely linked and coherent. These movements challenge the balance control system, which requires the human body to be aware of the body's position and maintain the center of gravity within a changing base of support. Previous studies have indicated that the practice of TCC can effectively improve balance because it can reinforce the sensorimotor system, lower extremity muscle strength, endurance, proprioception, and body awareness (31, 32). In view of the fact that a series of articles have reported that TCC can improve the balance function and other functional symptoms of a variety of populations, including core stability, posture control ability, and lower limb movement ability such as hip, knee, and ankle (16, 32). Thus, we hypothesized that both TCC intervention and CBT would obtain significant improvements of postural stability and self-reported outcomes in patients with FAI.

In addition, several studies have shown that decreased cognitive function may be associated with CAI and decreased postural control may be also related to altered cognitive processing (33, 34). Researchers (35) found that patients with CAI had relatively lower cognitive functions such as composite memory, visual memory, working memory, and attention compared to controls. Another study based on computerized neurocognitive testing showed that basketball players with CAI had slower reaction time, suggesting that CAI may be related to cognitive processing speed and accuracy (36).

TCC is a medium-intensity form of physical and mental exercise that involves cognitive activities such as movement recall, task switching, concentration, and visuospatial processing that are carried out simultaneously with physical movements. Previous studies have reported that TCC training can improve brain executive function, language function, learning and memory ability, and cognitive processing speed (37–39). As TCC is a combination of cognitive and motor tasks, we firmly believe in our hypothesis that 12-week TCC intervention has a positive effect on postural stability and self-reported outcomes in patients with FAI, with a possible superiority over CBT.

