**Discussion:**

This trial will demonstrate whether a 12-week TCC intervention positively affects postural stability and self-reported outcomes in patients with FAI. At the same time, the superiority of its clinical efficacy will also be compared with that of CBT. This study may also help to redefine the value of traditional Chinese exercises in the treatment of chronic ankle instability.

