As far as we know, only one research group has reported that TCC intervention has a positive effect on postural control and self-reported instability feeling in patients with CAI but failed to compare the clinical effects with other training programs (18). Moreover, there is no literature directly examining the comparative effects of TCC intervention and conventional balance training (CBT) protocols regarding their impact on postural stability and self-reported outcomes in patients with FAI. From the perspective of clinical utility, it is extremely interesting to see which intervention is more effective as clinicians always want to be able to select the best intervention for patients with FAI. Theoretically, patients with FAI are a series of complex clinical syndromes resulting from the interaction of pathomechanical, sensory perceptual, and motor behavior impairments (19, 20). Balance training alone may only achieve partial therapeutic effects. TCC is a kind of mind–body exercise that may be particularly beneficial to FAI because it involves movement recall, task switching, attention, and visuospatial processing simultaneous with physical movements (21). Therefore, our hypothesis is that both TCC intervention and CBT would obtain significant improvements, with a possible superiority of TCC over CBT. Thus, the aim of this randomized controlled study is to test the comparative effects of TCC intervention and CBT protocols in improving postural balance and subjective instability feelings in patients with FAI.

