## Methods and analysis

### Study design and setting

This study will be a single-center, randomized, exploratory trial with two parallel groups. The objective is to test the comparative effects of TCC intervention and CBT protocols in improving postural balance and subjective instability feelings in patients with FAI.

We recruited subjects from the Fujian Provincial Hospital, the surrounding Sports Center, and residents of Gulou District, Fuzhou City, Fujian Province, China. Potential eligible subjects who meet the following inclusion criteria but are excluded from the exclusion criteria will be determined by two orthopedic surgeons for eventual inclusion in the study. After signing the written informed consent form, eligible participants will be randomly divided into two groups, the intervention group or the control group, at a 1:1 ratio. All assessments will be conducted at baseline, post intervention, and 3-month follow-up. This study was designed in strict accordance with the Standardized Protocol Items, including the Recommendations for Interventional Trials (SPIRIT) Checklist, and has been approved by the Ethical Committee of Fujian Provincial Hospital (no. k2019-03-035). In addition, we have completed registration in the Chinese Clinical Trials Registry in 2021. The flow diagram for this trial is shown in Figure 1. The specific flowchart of participant recruitment is shown in Table 1.

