### Interventions

#### Control group

Subjects in the control group will receive CBT based on the Single-Legged Balance Training Program. The program consisted of a warm-up exercise, the single-legged stance, single-legged stance with bosu ball exercises, single-legged stance with kicking against resistance in four directions, and step-down with single-legged in four directions. The training difficulty of this exercise prescription is from easy to difficult. In the training process of this experimental study, the subjects were required to keep the body center of gravity stable during the training process, 40 min each time, 3 times a week for 12 weeks.

In addition to the CBT, all participants will receive health education at the start of the study and monthly throughout the study period. FAI is mainly characterized by recurrent “muscle weakness” of the ankle joint associated with ankle pain, muscle strength weakening, proprioception decline, and random control disorders of joint movement. Therefore, it is necessary to inform them of the preventive measures for ankle sprain, instruct them to properly rest, correct their bad exercise patterns (avoid acute jumping, climbing mountains, and other activities that damage joints), and wear ankle protection when necessary. In addition, patients with ankle joint injury are often anxious and corresponding psychological nursing can be carried out to relieve the anxiety and worry of patients.

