### Experimental group

On the basis of health education treatment in the control group, the TCC intervention group will undergo a 40-min 24 Simplified Yang-style TCC exercise. Yang-style TCC consists of slow, smooth, and rhythmic movements that emphasize the practitioner's focus on trunk rotation, weight shifting, coordination, and maintenance of lower limb posture stability. Subjects with FAI will be taught and supervised by an expert TCC coach to ensure the unity of practice time and the basic correctness of action rhythm. The complete set of TCC exercises consists of three parts: 5-min warmup, 30-min TCC practice, and 5-min cool down. Practice will occur once per day, three times a week for 12 weeks, for a total of 36 times.

During the whole training process, patients are encouraged to keep practicing if they have slight ankle pain. If the ankle joint pain of the subject is obvious during the training, i.e., VAS > 3 points, we will suggest the subject to rest or suspend the training, and continue after the pain is relieved.

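### The article promises the effect of Tai Chi itself and ties its primary outcome and power to before-after change, but only the Tai Chi versus balance-training contrast is identified by randomisation

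*Protocol article*

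**What the plan says.** The article describes its purpose in two ways.

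- **Comparative objective.** The abstract (Background), the end of the Background section and Study design and setting all give the aim as comparing Tai Chi (TCC) with conventional balance training (CBT).
- **Effect of TCC itself.** The abstract's Discussion says "This trial will demonstrate whether a 12-week TCC intervention positively affects postural stability and self-reported outcomes in patients with FAI", and the main Discussion says "This study aims to determine the effect of 12 weeks of TCC intervention on postural stability and self-reported outcomes in patients with FAI". In both places the comparison with CBT follows as an additional sentence. The last paragraph of the Discussion again separates a positive effect of TCC from a possible advantage over CBT.

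The Background adds a hypothesis about each arm: "our hypothesis is that both TCC intervention and CBT would obtain significant improvements, with a possible superiority of TCC over CBT". The Discussion repeats the part about both arms improving.

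The comparator is active: "Subjects in the control group will receive CBT based on the Single-Legged Balance Training Program". Education is not confined to one arm, since the same section says that "all participants will receive health education at the start of the study and monthly throughout the study period". The experimental arm receives that education plus supervised Yang-style TCC. Each arm trains for 40 minutes, three times a week for 12 weeks.

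Two operative sections are framed within arms. The CAIT section names the comparison of scores before and after treatment as the primary outcome measure. Sample size states that the power analysis rests on within-group differences in SEBT and CAIT. Data analysis names repeated-measures ANOVA for variables measured repeatedly.

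**The concern.** Randomisation identifies one quantity here: the difference between TCC and CBT, each given with health education. The change from baseline within an arm is an uncontrolled before-after comparison. It contains any training effect, but also:

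- natural recovery after a sprain;
- regression to the mean, because entry requires CAIT ≤ 25 and CAIT is also the primary outcome;
- monthly education, which covers rest, avoiding certain activities and wearing ankle protection;
- repeat testing on the questionnaires and the platform.

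If this were only loose prose in a Discussion it would matter little. It matters because the primary outcome and the power basis are also written as before-after quantities. Someone following the article as written could test each arm against its own baseline, find significance, and report that TCC works. If the two arms do not differ, before-after gains are the only thing left to support that claim, and they cannot support it.

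**Working it through.** **Inputs from the article.** SD of CAIT change 2.21 (intervention) and 2.10 (control); planned mean CAIT changes 10.8 and 0.2; 28 evaluable and 34 enrolled per arm; two-sided alpha 0.05 (all from Sample size). Minimum detectable change 3 points (CAIT section). **Assumptions.** A non-specific gain of 1.5 points, for illustration, and an SD of 5 as a pessimistic alternative. The article gives no figure for recovery, regression or practice effects.

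**1. The plan's own sample size.** The article states 28 per group for d = 0.8, two-sided 0.05, 90% power.
- Paired within-group t-test, two-sided: 19 per group. With 28 per group the power is 98.3%.
- Two independent groups, two-sided: 34 per group. With 28 per group the power is 83.6%.
- Two independent groups, one-sided: 28 per group (90.5%).

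So 28 does not reproduce as the within-group calculation described. It matches a one-sided between-group test, which is a separate matter. For this point, the text names within-group differences as the powered quantity, and a within-group test at these sizes passes easily.

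**2. Smallest observed within-arm gain that is significant** = t(0.975, n−1) × SD / √n.
- n = 34, SD 2.21: 2.0345 × 2.21 / 5.831 = 0.77 points.
- n = 28, SD 2.21: 2.0518 × 2.21 / 5.292 = 0.86 points.
- SD 2.10: 0.73 (n = 34) and 0.81 (n = 28).
- SD 5 (assumption): 1.74 (n = 34) and 1.94 (n = 28).

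At the article's SDs the threshold is under a third of the 3-point minimum detectable change.

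**3. Chance that a purely non-specific true gain is significant in the TCC arm** (noncentral t, noncentrality = gain × √n / SD).

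| True gain | SD | n = 28 | n = 34 |
|---|---|---|---|
| 0.2 | 2.21 | 7.5% | 8.1% |
| 0.5 | 2.21 | 21% | 25% |
| 1.0 | 2.21 | 64% | 73% |
| 1.5 | 2.21 | 93% | 97% |
| 1.5 | 5 (assumed) | 33% | 40% |

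For example, at gain 1.5, SD 2.21 and n = 28, the noncentrality is 1.5 × 5.292 / 2.21 = 3.59.

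**4. Both arms, same non-specific gain.** A simulation of 40,000 trials (28 per arm, SDs 2.21 and 2.10) at a gain of 1.5 finds both arms significantly improved in 89%. The product of the two single-arm powers agrees: 0.933 × 0.954 = 0.89. In the same simulation the TCC versus CBT test is significant in 4.8%, close to its nominal 5%. A shared non-specific gain cancels in the randomised contrast and does not cancel in either before-after test.

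**The case against.** **The stated objective in Methods is already comparative.** This is correct. The objective in Study design and setting is TCC versus CBT, and the randomised comparison is unharmed. A reader might infer that the trial cannot answer its main question, and the article does not support that. What remains is that other sections promise more, and that the primary outcome and power basis follow the before-after reading.

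**Improvement in both arms is a hypothesis, not an aim, and it can be tested.** This also stands. Whether scores rise from baseline is testable. Attribution of the rise to the training is what fails.

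**Superiority over CBT would support TCC indirectly.** This is fair, since the Discussion treats CBT's benefit as established. The route closes if the arms do not differ, because the article states no equivalence or non-inferiority margin.

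**No passage says a null difference will be read as efficacy or equivalence.** True. A reader might infer such an intention, but the article contains none. The point is that it does not rule the reading out while its aim and outcome definition invite it.

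**A statistical analysis plan could settle this.** It could name the ANOVA effect of interest. It would not by itself change the aims, hypothesis, primary outcome and power basis fixed in this article.

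**Conclusion.** The concern holds in limited form. The article states the effect of TCC itself as something the trial will determine, and frames its primary outcome and power around within-arm change, while the two-active-arm design identifies only TCC minus CBT. A before-after gain of 1.5 points owing nothing to either programme would be declared significant within the TCC arm in 93% to 97% of trials at SD 2.21. This rests on the article's planning SD applying to this population; at an assumed SD of 5 the figure is 33% to 40%, still well above 5%.

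Two stronger readings are not supported. One is that almost any non-specific gain would confirm the hypotheses: an observed gain below about 0.8 points would not normally reach significance, and a true gain of 0.2, the planning value for control, would do so in only about 8% of trials. The other is that the abstract contradicts "This study will be a single-center, randomized, exploratory trial with two parallel groups": the abstract poses an open question (whether TCC helps), which does not clearly conflict with an exploratory design.

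**What to change.** 1. In the abstract's Discussion, the Background hypothesis and the Discussion (including its last paragraph), align the wording with the objective already given in Methods: TCC compared with CBT, each with health education.
2. In Sample size and the CAIT section, define the primary comparison as the between-group difference in CAIT change, and identify it in Data analysis as the group-by-time effect of the repeated-measures ANOVA.
3. State that within-arm changes are descriptive and will not support a claim that TCC or CBT is effective.
4. State that a non-significant difference will not be read as efficacy or as equivalence. The 3-point figure should not be pressed into service as an equivalence margin: the article gives it as a minimum detectable change and offers no justification for the other use.

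This changes wording only and adds no participants, visits or procedures. The cost is a narrower headline claim. A claim about TCC itself would need an education-only or untreated comparator, which is a different trial.

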## Trial status

Protocol number: version 2.0, 20 January 2021. Recruiting start date: 5 November 2022. Expected study completion date: December 2025. In case of any changes to the protocol, we will notify the relevant parties (investigators, participants, etc.) through email or letter.

## Ethics statement

The studies involving human participants were reviewed and approved by the Ethics Board of Fujian Provincial Hospital (K2019-03-035). The patients/participants provided their written informed consent to participate in this study.

## Abbreviations

FAI: functional ankle instability
CAI: chronic ankle instability
TCC: Tai Chi Chuan
CBT: conventional balance training
CAIT: Cumberland Ankle Instability Tool
SEBT: Star Excursion Balance Test
AOFAS-AHES: American Orthopaedics Foot and Ankle Society's Ankle-Hindfoot Evaluation Scale
SPIRIT: Standardized Protocol Items, Recommendations for Interventional Trials
SF-36: the MOS item Short Form Health Survey
AEs: adverse events
SAE: serious adverse event
COP: center of pressure
ATE: average trace error
RA: research assistant
DSMB: Data and Safety Monitoring Board
CRFs: case report forms
SOPs: standard operating procedures
CONSORT: Consolidated Standards of Reporting Trials
SD: standard deviation
GEE: generalized estimation equations.
